***Training of research staff***

Main field project staff in each country will be trained in the ENERGY meeting in Athens April 13-15 2011. Remaining field project staff will be trained by main country responsible within each country.

**Data management**

***Identification***

In order to merge data from the different surveys, it is of utmost importance that the different data sources are marked with a unique ID for every participant. Parents have the same ID number as their children. Every country/partner has to keep an ID-key, i.e. a list of participating names including every child’s unique ID number. This list has to be kept separately from the data files.

The unique ID numbers (always 7 digits) follow this code:

- Country number: 1 digit (Belgium = 1, Germany = 9, Greece = 2, Hungary = 3, Norway = 5).
- School number (within country): 2 digits (intervention schools will be given numbers from 01-10, control schools will be given numbers from 11-20)
- Class level: 2 digits (5, 6 or 7– corresponding to grade level, and 1, 2 etc for separating classes in same grade level (i.e. 51 is grade 5 class A, 52 is grade 5 class B)
- Child number: 2 digits

Example ID 9026213: 9=Germany, 02=German school no. 2, intervention school, 62=6th grade, class B, 13=pupil no. 13 in that class.

The ID will be the same for the child and the parent questionnaires and child accelerometer data. An audit instrument and school management questionnaire will be given an ID based on country and school. The teacher process evaluation questionnaires will be given an ID based on country, school and class (i.e. one teacher per intervention class).

***Data entry***

Each partner/country is responsible for entering all collected data into SPSS. UiA will provide pre-coded SPSS templates, including definition of values to be given each answering alternative in all questions for all different surveys, in which the data must be entered. Each country/partner decides whether to manually insert the data, or to do it by optical scanning.

For all questions where only one tick is allowed (i.e. most questions) the coding is always like this: 1st answering alternative=1, 2nd answering alternative=2, 3rd answering alternative=3, 4th answering alternative=4 and so it goes. Missing is always coded -9. When two neighbour boxes are both ticked, or a tick is in between two boxes, choose the most conservative estimate (i.e. the alternative closest to the middle). If the two alternatives are both equally close to the middle choose one of them at random. If three or more ticks, or two ticks that are further apart than the closest box, answer is coded as missing.

For questions where multiple ticks are allowed, every answering alternative is a separate variable where a tick is coded 1 and not a tick is coded 0. However, if there are no ticks in any of the answering alternatives all variables/answering alternatives will be coded -9 (missing).

For questions with written numbers just fill in the number written. NB. there are two variables for each sleep question: (a) Hours and (b) Minutes.

Raw data (as non-personal identifiable SPSS files) will be sent UiA by e-mail as soon as they are ready.

***Data cleaning***

Each partner/country is responsible for cleaning their data.

To ensure that the data has been entered correctly in the child and parent questionnaires a total of 5% of all hand inserted child and parents questionnaire will be entered a second time (in a separate file) (not needed if the data are scanned). If >3% of the data differs, all questionnaires have to be re-entered. Also 20% of the audit instrument and the school management questionnaires will be re-entered, and differences will be assessed.

All variables must be checked in order to certify that all values are within the defined ranges for the separate variables. If values are outside min-max range the questionnaire must be checked and values be replaced with the correct values.

Cleaned non-personal identifiable SPSS files will be sent UiA by e-mail.

***Data recoding and restruction***

This will be done by UiA based on the recoding and restruction conducted in WP7. A final SPSS file will be sent to all partners, and also VUmc for central data storage.

**Data interpretation**

The outcome evaluation will be based on a set of multilevel (i.e. adjusted for school) regression analyses on differences between intervention and control groups on post-test values, as recommended by Twisk and Proper (*J Clin Epidemiol* 2004, **57:**223-228), adjusted for baseline values and sex. Separate similar analyses will be conducted for parents (only including parents answering both the pre-test and post-test questionnaire). For the process evaluation descriptive analyses will be presented.

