**Concept**

Research has shown that the number of children affected by overweight and obesity is now rising at more than 400,000 a year and already affects almost one in four children across Europe.

Overweight and obesity are the result of health behaviours related to nutrition and physical activity causing a positive energy balance; when energy intake through nutrition exceeds energy expenditure, a positive energy balance will result to weight gain. It is less clear which specific dietary, sedentary and physical activity behaviours contribute to excess weight gain in different populations.

ENERGY is a unique project, which for the first time will systematically assess modifiable determinants of energy-balance health behaviours and address the promotion of these behaviours in a European-wide setting.

The main objective of ENERGY is to build a school based, family involved intervention scheme for the promotion of health behaviours that contribute to obesity prevention in children aged 10-12 years old across Europe.

The objective of WP9 is to (1) Conduct a process and outcome evaluation of the intervention, and (2) translate the evaluation results into practical input for WP10 (see Appendix 1).

The intervention scheme was made as part of WP8, and specifically aims at reducing sitting time in school and at home (with special emphasis on TV and PC/electronic games).

The present protocol describes the background and practical procedures for the evaluation study that will be carried out during the fall in 2011 by partners in five different European countries; Belgium, Germany, Greece, Hungary and Norway.

The ENERGY project is supported by the European Commission and is funded by the Seventh Framework Programme (CORDIS FP7) of the European Commission, HEALTH.

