**Sampling procedure**

***Study design***

In order to evaluate the effectiveness of the intervention, the intervention will be tested in a pre-test post-test design including an intervention and a control condition. The control condition will not implement the intervention, but will continue the usual school curriculum. Schools will be the level of randomisation, within each country, in order to prevent contamination of intervention activities.

From each country at least 10 schools with at least 2 classes each (25 children per class on average) will participate in the evaluation study, resulting in total in about 2500 participating children (500 per country). Power calculations based on data from the WP7 cross sectional survey indicate that this sample size is sufficient to detect a 20% decrease in total screen time.

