***School sample***

A convenient sample of at least 10 schools in each country will be selected; i.e. schools close to the University or in other convenient areas. In order to be included, each school must have at least 50 10-12 year olds to result in a study sample of at least 500 pupils in each country. The schools will be paired according to size (and also sex and socio economic status if necessary and possible) in order to get similar intervention and control groups. Then one school in each pair will be randomly drawn to the intervention group, and the remaining school will be the control school, by project co-ordinator (VUmc Amsterdam; a partner that will not conduct this evaluation study).

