***Study sample***

The study population will be all pupils from the two grade levels that include the majority of pupils born in years 1999 and 2000 (most will be 10-12 year old during fall 2011), and one of their parents. At least two classes per school (one per grade level), with 25 pupils/class should be included in each participating school. All pupils within included classes are invited to participate. However, student participation rate will not be 100%, and over-sampling is needed. Based on the experiences from the cross sectional study in WP7, in which pupil participation rate varied largely with country, each country has to over-sample country specific in order to reach a study sample of 500 (defined by pupils responding to both the pre and the post questionnaire survey).

Over-sampling should firstly be done by adding more classes per school. It is important to always include similar number of classes per school from the two different grade levels included in the study in order to not alter the age level between intervention and control schools. Secondly, add more schools. It is important to always include schools in pairs, in order to have a similar number of intervention and control schools.

In most countries it appears that including four classes per school (in ten schools) is needed in order to reach a final study sample of 500.

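### The outcome model leaves out country, the stratum within which schools are randomised, so any country differences left after baseline adjustment inflate the standard error and cost power

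*Protocol*

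**What the plan says.** Randomisation is by school and is stratified. Study design states: "Schools will be the level of randomisation, within each country, in order to prevent contamination of intervention activities". School sample adds a finer layer. It says "The schools will be paired according to size", with sex and socio-economic status as further pairing factors where needed and feasible, and then: "Then one school in each pair will be randomly drawn to the intervention group, and the remaining school will be the control school". Study sample requires added schools to come in pairs too, so the arms stay equal in number.

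The study is run by "partners in five different European countries; Belgium, Germany, Greece, Hungary and Norway". On size, Study design says: "From each country at least 10 schools with at least 2 classes each (25 children per class on average) will participate". It gives the sample as a pooled total of about 2500, with 500 per country.

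Data interpretation describes the outcome model. Post-test values are compared between arms in a multilevel regression that takes account of school, "adjusted for baseline values and sex". Parents get a separate, similar analysis. Neither country nor pair is mentioned, and no section says that the analysis is done country by country.

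**The concern.** The design groups schools by country before randomising, and the stated analysis ignores that grouping. Stratified randomisation removes differences between strata from the comparison of arms. The analysis benefits only if it removes them from the error term as well. Otherwise the trial has the precision but does not report it.

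Country cannot be assumed to be absorbed by the school term. The intervention is assigned to whole schools, so school has to be a random effect, and a single school variance then contains whatever country variance is left.

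Some remainder after baseline adjustment is plausible from the protocol itself. Each partner translates its own questionnaires (Questionnaire surveys), each country sets its own calendar (Time needed), and staff are asked to limit their interaction with pupils because of variation between countries (Procedures at the survey day). At stake is power for the main comparison, not its validity.

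**Working it through.** **Inputs from the protocol.** 5 countries, 10 schools per country, 2 classes per school, 25 children per class; one school of each pair to each arm, hence 5 v 5 schools per country.

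**The plan's own figure.** 5 × 10 × 2 × 25 = 2500, which agrees. The accompanying statement that this suffices to detect a 20% fall in screen time cannot be checked, because no mean, SD, ICC, alpha or power is given.

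**Assumptions (not in the protocol).** 50 schools with m = 50 pupils each; residual variance within country, after baseline and sex, equal to 1; school ICC 0.03, 0.05 or 0.10; residual between-country variance Vc from 0 upwards.

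**Step 1: true variance of the effect.** Let w = ICC + (1 − ICC)/m be the variance of a school mean within country. With 25 v 25 schools balanced 5 v 5 in every country, country effects cancel, so Var(effect) = (4/50)·w whatever Vc is.

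**Step 2: what each model reports.**
- With country fixed, the between-school mean square has expectation w on 50 − 5 − 1 = 44 df.
- Without country, the 4 country df, each with expectation w + 10·Vc, are pooled with those 44. The expectation is [44w + 4(w + 10Vc)]/48 = w + (40/48)·Vc on 48 df.
- SE ratio, without versus with country: √[1 + (40/48)·Vc/w].

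**Step 3: numbers.**
- ICC 0.03: w = 0.03 + 0.97/50 = 0.0494. Vc = 0.01 gives √(0.0577/0.0494) = 1.081; Vc = 0.03 gives √(0.0744/0.0494) = 1.227.
- ICC 0.05: w = 0.05 + 0.95/50 = 0.069. Vc = 0.01 gives √(0.0773/0.069) = 1.059.
- ICC 0.10: w = 0.10 + 0.90/50 = 0.118. Vc = 0.01 gives √(0.1263/0.118) = 1.035.
- Vc = 0 gives 1.00 in every case.

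**Step 4: simulation of school means.** 20,000 replicates per setting, with the true effect set so that the model with country has about 80% power; two-sided nominal 5%.

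| ICC | Vc | Mean SE without / with country | Type I error without country | Power without / with country |
|---|---|---|---|---|
| 0.03 | 0 | 0.0624 / 0.0624 | 5.06% | 80.2% / 80.0% |
| 0.03 | 0.01 | 0.0676 / 0.0625 | 3.45% | 75.1% / 79.6% |
| 0.03 | 0.05 | 0.0838 / 0.0625 | 1.36% | 57.2% / 80.4% |
| 0.05 | 0.01 | 0.0782 / 0.0738 | 3.90% | 77.0% / 80.3% |
| 0.05 | 0.05 | 0.0930 / 0.0739 | 1.94% | 63.3% / 80.3% |
| 0.10 | 0.01 | 0.1000 / 0.0966 | 4.17% | 78.0% / 79.9% |
| 0.10 | 0.05 | 0.1120 / 0.0966 | 2.51% | 69.9% / 80.0% |

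A separate run of 6,000 replicates at ICC 0.03 and Vc = 0.03 gave mean SEs of 0.076 and 0.062, type I error 1.9%, and power 65% against 80%. At ICC 0.05 the empirical SE of the effect stayed between 0.0738 and 0.0748 for every Vc from 0 to 0.10. That matches the model with country and confirms Step 1.

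**The case against.** The strongest reply is that the harm is conditional. The model already adjusts for each pupil's own baseline value on the same items. If that absorbs all stable country differences, Vc is nil and so is the loss. A larger school ICC also shrinks it: at Vc = 0.01 and ICC 0.05 to 0.10 the inflation is only 3.5% to 5.9%. This stands, and the size should be given only as a range.

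It can also be said that Data interpretation is a short summary and that a statistical analysis plan might add country. That is possible. But the section names a clustering level and a covariate list, and the list as written leaves out the randomisation stratum. Separate analyses by country would make the term unnecessary, but the protocol does not announce them and states its sample size as a pooled total.

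A reader might infer more than the document supports in three ways:
- **Grade.** Study sample keeps class numbers per grade similar in every school, "in order to not alter the age level between intervention and control schools", so grade may look like a second missing stratum. It is not a factor in the randomisation. With an equal split in each school it does not move school means relative to one another. A grade difference of g SD adds about g²/4 to pupil-level variance (0.01 at g = 0.2) and leaves the between-school mean square unchanged. The standard-error argument rests on country alone.
- **Bias or false positives.** Neither follows. Arms are balanced within country, and the error goes in the conservative direction.
- **A larger inflation.** Adding the whole of Vc to w would give √(0.0594/0.0494) = 1.10 and √(0.0794/0.0494) = 1.27. That overstates the effect, because only 4 of the 48 df carry country variance.

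It is also fair to say that the pair, not country, is the finest stratum, and that pair is absent too. Country recovers the main one. Fixing all 25 pairs would leave 50 − 25 − 1 = 24 df.

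**Conclusion.** The point holds for country. Schools are allocated within country, the stated model omits country, and any country variance remaining after baseline adjustment is counted as school noise. The consequence is an overstated standard error, a conservative test and lost power.

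The size cannot be fixed from the protocol. Under the assumptions above it runs from nothing at Vc = 0, through 3.5% to 8.1% on the standard error at Vc = 0.01, to about 23% at Vc = 0.03 with ICC 0.03. These figures assume equal school sizes. Unequal sizes or parental non-response make the balance approximate but do not change the direction. The change is worth making because it costs almost nothing even when Vc is zero, but the omission does not undermine the trial's validity.

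**What to change.** In Data interpretation, add country as a fixed effect (4 df) to the adjustment list, alongside school (random), baseline value and sex. Apply it to the pupil, parent and accelerometer analyses.

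Grade is at most an optional covariate in the pupil and parent models. It must not be entered with country in the accelerometer subsample. Under Accelerometer measurements, that subsample takes only the highest participating grade in each country, so grade is constant within country and cannot be estimated beside it.

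The cost is one phrase of wording and a fall from 48 to 44 school-level df. In the simulation with no country variance at ICC 0.03, power was 80.0% with country and 80.2% without. No new data are needed, because the country code is the first digit of the seven-digit ID under Identification.

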**APPENDIX 1 – From Grant agreement Annex I - “Description of Work”**
